### Statistical analysis

The difference in mean OKS between the groups at one year will be estimated using analysis of covariance (ANCOVA) to adjust for baseline OKS at randomisation (that is, at six weeks). The results will be presented as an adjusted mean difference with its corresponding 95% confidence interval. The principal analysis will be on an intention to treat basis where participants will be analysed according to the allocated group using all available data. Additional summary statistics will also be presented for change in OKS from pre-operative values.

Health economic analysis will compare the cost-effectiveness (over one year) of providing targeted additional physiotherapy to those patients defined as performing poorly after six weeks against standard care. A cost-utility analysis (calculation of incremental costs per quality adjusted life year (QALY) gained) will be performed from the NHS perspective in line with the preferred method by NICE [22]. Resource use estimates from the study will be combined with unit costs taken from standard costing sources to produce an estimate of the cost to the NHS of providing the treatment. Health benefits in terms of QALYs will be derived from the standard UK tariff for the EQ-5D [25]. Estimates of NHS cost and QALYs will then be combined to produce an incremental cost-effectiveness ratio. This ratio will be presented using probabilistic sensitivity analysis [26] with deterministic analysis used on key modelling assumptions.

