### Randomisation procedures

Randomisation will be carried out using a bespoke web-based randomisation protocol. Patients will be randomised on a 1:1 ratio to either ‘standard of care physiotherapy’ or ‘enhanced physiotherapy’. Randomisation will be stratified by centre with block allocation.

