### Sample size calculation

The sample size for TRIO is 400 patients (200 per arm). This was determined from previous research. The power calculation (Table 3) is based on the accepted change in the OKS that is considered clinically significant and of interest when comparing interventions (3 points) [16]. Typical one year change scores for the OKS are 16 points with a reported standard deviation of 9.2 [3,4].

**Table 3 T3:** Power calculation

**Difference**	**Size**	**Power**
3	150	80%
3	200	90%

Two-sample *t*-test, alpha = 0.05 (two-sided), assumed SD = 9.2.

A large prospective cohort is required to achieve the desired numbers of poorly functioning knees; therefore the study will recruit from multiple major centres. Based on reported poor outcome rates of approximately 20%, and allowing for a potential of up to 20% of eligible patients being unwilling to be randomised, we aim to screen 2,750 patients prospectively at the six-week post-surgical review to identify 550 eligible, poorly functioning patients and to achieve recruitment (randomisation) of 440. Allowing for a further 10% loss to follow-up in the RCT will yield the 400 patients we require.

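### Randomisation is stratified by centre, but the stated primary ANCOVA names only six-week OKS; if centre is prognostic, the confidence interval is slightly too wide and the test slightly conservative

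*Protocol article*

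**What the plan says.** Under Randomisation procedures: "Patients will be randomised on a 1:1 ratio", and "Randomisation will be stratified by centre with block allocation". Centre is the only stratification factor given.

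Under Statistical analysis, the difference in mean OKS at one year is to be "estimated using analysis of covariance (ANCOVA) to adjust for baseline OKS at randomisation (that is, at six weeks". Of the output, the article says: "The results will be presented as an adjusted mean difference with its corresponding 95% confidence interval". Six-week OKS is the one covariate named, and the paragraph does not mention centre.

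Under Sample size calculation, the target difference is the one "considered clinically significant and of interest when comparing interventions (3 points" on the OKS. Table 3 assumes a two-sample t-test with "alpha = 0.05 (two-sided), assumed SD = 9.2". The required number is given as follows: "The sample size for TRIO is 400 patients (200 per arm". The article gives neither the number of centres nor any between-centre variance or ICC.

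**The concern.** Blocked 1:1 allocation within centre makes the arms nearly equal in size at every site. Differences between centres in average outcome then largely cancel out of the treatment comparison, so the true sampling variance of the difference excludes them. A model without centre does not recognise this. It leaves the between-centre variation in the residual and reports a standard error that includes it.

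If centre is prognostic, the primary 95% interval covers more often than 95%, the test rejects less than 5% of the time under the null, and some power is lost that the design had already secured.

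The article gives some reason to expect a centre effect. Under Study design, patients receive the local standard operation and immediate post-operative pathway before they enter the trial, and the sponsor chose centre as its stratification factor.

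**Working it through.** **Inputs from the article:** difference 3 points, SD 9.2, two-sided alpha 0.05, 200 per arm (Sample size calculation and Table 3); 1:1 allocation in blocks within centre (Randomisation procedures).

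**Assumed:** the centre ICC of one-year OKS that remains after adjustment for six-week OKS, taken as 0 to 0.10 because the article gives none.

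**Step 1: reproduce the stated power.** SE = 9.2 × sqrt(2/200) = 0.920. Power = Φ(3/0.920 − 1.96) = 90.3%, against 90% stated. With 150 per arm the same formula gives 80.6%, against 80% stated. Both reproduce.

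**Step 2: standard error with and without centre.** With balance within centre:
- SE reported without centre = SD × sqrt(2/n)
- true SE, which the model with centre estimates = SD × sqrt(2/n) × sqrt(1 − ICC)
- inflation = 1/sqrt(1 − ICC)

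**Step 3: consequences.**
- actual alpha without centre = 2Φ(−1.96/sqrt(1 − ICC))
- power without centre = Φ((3 − 1.96 × reported SE)/true SE)
- power with centre = Φ(3/true SE − 1.96)

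For example, at ICC 0.10 the true SE is 0.920 × sqrt(0.90) = 0.873. Power without centre is Φ((3 − 1.803)/0.873) = 91.5%. Power with centre is Φ(3/0.873 − 1.96) = 93.0%.

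| Assumed ICC | SE without → with centre | Inflation | 95% CI half-width | Actual alpha without centre | Power without → with centre |
|---|---|---|---|---|---|
| 0 | 0.920 → 0.920 | 0% | 1.80 → 1.80 | 0.050 | 90.3% → 90.3% |
| 0.02 | 0.920 → 0.911 | 1.0% | 1.80 → 1.79 | 0.048 | 90.6% → 90.9% |
| 0.05 | 0.920 → 0.897 | 2.6% | 1.80 → 1.76 | 0.044 | 90.9% → 91.7% |
| 0.10 | 0.920 → 0.873 | 5.4% | 1.80 → 1.71 | 0.039 | 91.5% → 93.0% |

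**Step 4: sensitivity to the number analysed.** The article says: "Allowing for a further 10% loss to follow-up in the RCT will yield the 400 patients we require". Taking 10% off 440 leaves 396, or 198 per arm. At ICC 0.10 power is then 91.2% without centre and 92.8% with it, a loss of 1.6 points against 1.5 at 200 per arm. At ICC 0 power is 90.05%. The conclusion does not change.

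**Step 5: sensitivity to the gain from six-week OKS.** The figures above use the full SD of 9.2, although the planned ANCOVA also removes what six-week OKS explains. If the two scores correlate 0.3 (an assumption), power at ICC 0.10 is 93.8% without centre and 95.0% with it. At a correlation of 0.5 it is 97.2% and 97.8%. The alpha figures are unchanged, because the ICC is defined on the residual. The power loss shrinks.

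**Step 6: check by simulation.** The closed form assumes exact balance among the patients analysed. A simulation relaxed that, with 10 centres and blocks of 4 (both assumed), 440 randomised, 400 analysed after random loss, and 3,000 runs per scenario. At ICC 0.10 the mean SE was about 0.915 without centre and 0.874 with it, type I error was 0.041 and 0.048, and power was 92.4% and 94.3%. The Monte Carlo standard error of a 5% rejection rate is sqrt(0.05 × 0.95/3000) = 0.4 percentage points, so this agrees with the closed form in direction and size.

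**The case against.** **The article does not exclude centre.** It says what the ANCOVA adjusts for without saying that nothing else enters, and a condensed article may leave the handling of stratification factors to an analysis plan not shown. This stands in part: that plan may already include centre. But the article does not merely stay silent. It states the primary model, its adjustment variable and the quantity to be reported, and a reader would take that as the model. If the analysis plan adds centre, the two documents should be brought into line.

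**The loss is conditional.** This stands in full. With no residual centre effect nothing is lost, and the article gives no ICC to show that there is one.

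**Variation in physiotherapy provision is weak evidence.** A reader might infer a strong centre effect from the remark under Study design that provision varies across the UK. The same paragraph says the control arm was standardised for that reason, and the Intervention section specifies the exercises in the enhanced arm. That remark therefore carries little weight. The local surgical and early-care pathway, which the trial does not standardise, is the better argument.

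**Secondary outcomes.** The article names no model for the secondary clinical outcomes, so it fixes nothing wrongly there. The point is confined to the primary analysis.

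**The effect is small.** This also stands. At ICC 0.05 the interval half-width changes by about 0.05 points, against a 3-point target.

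**Conclusion.** The point holds as a minor, conditional one. The stated primary model omits the factor on which randomisation is stratified. Over an assumed residual ICC of 0 to 0.10, this inflates the reported standard error by 0 to 5.4%, puts the actual two-sided alpha between 0.050 and 0.039, and costs 0 to about 1.6 percentage points of power. These figures rest on the assumed ICC, near-equal allocation within each centre among those analysed, and SD 9.2.

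A reader might go further and infer that the primary interval is certainly too wide, that the benefit of stratifying is lost, or that the primary result is unreliable. The article supports none of these. Whether the interval is too wide depends on a centre effect that is not quantified. The treatment estimate remains balanced on centre and unbiased, and only its reported precision is understated. Type I error does not exceed 5%, and the stated 90% power is met at every ICC considered.

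**What to change.** State the primary model as an ANCOVA of one-year OKS on allocated arm, six-week OKS and centre. Enter centre as a random intercept, or as a fixed effect with very small centres pooled by a rule set in advance. If the analysis plan already does this, bring the published description into line with it.

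Specify it before outcome data are seen, so that the choice cannot look data-driven; the article's Trial status section says recruitment was still under way at submission. The cost is one sentence and a few degrees of freedom out of about 400 observations. No new data are needed and the sample size does not change. If centre proves not to be prognostic, the loss is negligible: in the simulation at ICC 0 under the 3-point difference, the mean SE was 0.921 with centre and 0.920 without.

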### Inclusion criteria

1. Patients undergoing primary TKA for osteoarthritis.

2. Defined poor outcome (OKS less than or equal to 26) at first post-operative review (six weeks).

3. Patients are able to consent and willing to comply with the study protocol.

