### Study assessments

All the study centres involved in this project collect routine baseline data using the OKS and EQ-5D. These data will be accessed retrospectively for recruited patients at the individual centres.

At the study baseline (six weeks post-operation) an OKS will be completed and eligible patients consented and randomised. Once consent has been obtained, the additional trial Health Economics Questionnaire and EQ-5D questionnaire will be completed. Physiotherapy pre-intervention assessment will occur two weeks following this (and TUG test performed). Following either study intervention, all patients will have a second (post-intervention) physiotherapy review (OKS, TUG, EQ-5D and Health Economics Questionnaire). At six months and one year post-operation, the OKS, EQ-5D, Health Economics and Satisfaction questions will be assessed by postal questionnaire (Table 2).

**Table 2 T2:** Study assessments by time point

**Time point**	**Pre-operation**	**6 weeks**	**8 weeks**	**14 weeks**	**6 months**	**1 year**
OKS	X	X		X	X	X
EQ-5D	X	X		X	X	X
Patient demographics		X				
Pain score VAS		X		X	X	X
Health economics questionnaire		X		X	X	X
TUG			X	X		
Satisfaction questionnaire					X	X

Trial baseline is at six weeks post-operation. Pre-operative data will be accessed retrospectively. Assessment timeframes are calculated from the date of surgery.

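### Optional efficiency gain: pre-operative OKS, planned for descriptive use only, could join the range-restricted six-week OKS as a covariate in the primary ANCOVA

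*Protocol article*

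**What the plan says.** All places are in the Protocol article, Methods/Design.

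- **Statistical analysis.** One-year OKS is compared between arms by ANCOVA adjusted for OKS at randomisation, which is the six-week score. No other covariate is named. On the pre-operative score the section adds only: "Additional summary statistics will also be presented for change in OKS from pre-operative values".
- **Inclusion criteria.** The six-week score also decides entry: "Defined poor outcome (OKS less than or equal to 26) at first post-operative review (six weeks"). Study design gives the scale as 0 to 48.
- **Study assessments.** "All the study centres involved in this project collect routine baseline data using the OKS and EQ-5D". The section plans retrospective access to these data for recruited patients, and Table 2 lists a pre-operative OKS. Completeness is not stated.
- **Randomisation procedures.** Allocation is 1:1 in blocks, stratified by centre.
- **Sample size calculation.** A two-sample *t*-test with "alpha = 0.05 (two-sided), assumed SD = 9.2", a difference of 3 points, and 80% power at 150 or 90% at 200 per arm. The SD is sourced as follows: "Typical one year change scores for the OKS are 16 points with a reported standard deviation of 9.2". About 20% of screened patients are expected to qualify, and 440 are to be randomised with 10% loss.

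**The concern.** An ANCOVA gains precision in proportion to how much outcome variance its covariates explain. Here the one named covariate is also the selection variable. Admitting only low scores compresses its range and weakens its correlation with one-year OKS within the trial.

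Pre-operative OKS uses the same instrument, is measured before randomisation and is not cut directly by the entry rule. The article considers this score and assigns it to summaries while naming a different covariate for the primary model. That is a stated choice that can be reviewed, not a detail merely left out.

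What is at stake is the width of the confidence interval for the primary estimate. The sample has little slack: 440 less 10% leaves 396, or 198 per arm, which is the number that 90% power requires under the plan's assumptions.

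**Working it through.** **1. The plan's own figures.** Inputs from Sample size calculation: difference 3, SD 9.2, two-sided alpha 0.05. Normal approximation: power = Φ(3 / (9.2·√(2/n)) − 1.960).

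- n = 150 per arm: 3/1.0623 = 2.824; Φ(0.864) = 80.6%.
- n = 200 per arm: 3/0.92 = 3.261; Φ(1.301) = 90.3%.
- n per arm for 90%: 2·(1.960 + 1.282)²·9.2²/3² = 197.6, so 198.

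The stated 80% and 90% are reproduced. They rest on an unadjusted test and claim no gain from any covariate.

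**2. Range restriction of six-week OKS.** Input: about 20% qualify. Assumption: the six-week score is normal in all patients and recruits are its lowest 20%.

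- Cut point a = −0.842; λ = φ(a)/0.20 = 1.400.
- Variance ratio = 1 − aλ − λ² = 0.219; SD ratio u = 0.468.
- Restricted correlation = r·u / √(1 − r² + r²u²).

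| Assumed unselected r with one-year OKS | r among recruits | R² among recruits |
|---|---|---|
| 0.4 | 0.20 | 0.04 |
| 0.5 | 0.26 | 0.07 |
| 0.6 | 0.33 | 0.11 |

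At r = 0.5, R² falls from 0.25 to 0.07.

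**3. Indirect restriction of pre-operative OKS.** If it correlates c with six-week OKS, its SD ratio among recruits is √(1 − c²(1 − 0.219)). For assumed c of 0.3 and 0.5 this is 0.96 and 0.90. It is narrowed too, but only mildly.

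**4. What pre-operative OKS could add.** The standard error is multiplied by √(1 − p²), where p is the partial correlation of pre-operative with one-year OKS given six-week OKS. The article does not give p. From assumed unselected correlations, with a = pre-operative/six-week, b = six-week/one-year and d = pre-operative/one-year:

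p = (d − ab) / √((1 − a²)(1 − b²))

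Over a = 0.3 to 0.5, b = 0.4 to 0.6 and d = 0.2 to 0.4:

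- Least gain, for example a = 0.4, b = 0.5, d = 0.2: p = 0, no gain.
- Greatest gain, a = 0.3, b = 0.4, d = 0.4: p = 0.28/√(0.91·0.84) = 0.320; p² = 0.103; standard error ratio 0.947, a fall of 5.3%.

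Partial R² therefore runs from 0 to about 10%. Under joint normality, selection on the six-week score leaves p unchanged. The restriction in step 2 weakens the named covariate; it does not raise the proportional gain from the second one.

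**5. Power at 198 per arm**, treating 9.2 as the residual SD before pre-operative OKS is added. Without it, 3/(9.2·√(2/198)) = 3.245.

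| Partial R² (assumed) | Fall in SE | Power | Equivalent analysed total, 396/(1 − R²) |
|---|---|---|---|
| 0 | 0 | Φ(1.285) = 90.0% | 396 |
| 5% | 2.5% | Φ(1.369) = 91.4% | 417 |
| 10% | 5.1% | Φ(1.460) = 92.8% | 440 |

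The fall in standard error and the equivalent total do not depend on 9.2. The power figures do.

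**The case against.** The strongest reply is that nothing here is wrong. ANCOVA on the outcome instrument measured at randomisation is standard, valid and unbiased, and the power claim does not lean on it. Chance imbalance in pre-operative status is covered in expectation by randomisation and reflected in the confidence interval. The article condenses a fuller protocol, and an analysis plan not shown may add covariates. All of this stands, and it makes the point an improvement rather than a correction.

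Four stronger readings are tempting and not supported:

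- *Precision is demonstrably lost.* This needs the partial correlation, which the article does not give. It could be zero.
- *The pre-operative score is held for every recruit.* The article says it is collected routinely and will be retrieved; it does not say how complete it is.
- *Only the six-week score is restricted.* Selection narrows the pre-operative score as well, though mildly (step 3).
- *The power gain follows from the plan's SD.* The 9.2 is the SD of typical one-year change scores, presumably measured from pre-operative values, and not a residual SD after six-week adjustment in slow recoverers. If pre-operative OKS is already subtracted in that figure, reducing it again for the same score counts it twice.

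One consideration runs the other way. Within one population, ANCOVA on pre-operative OKS cannot have a larger residual SD than the change score, and ANCOVA on the six-week score alone has no such guarantee. Because 9.2 describes typical patients, this supports the direction of the suggestion but does not settle its size.

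**Conclusion.** The point holds as a recommendation on efficiency. The design facts are firm: six-week OKS is the only covariate named, entry restricts it by design, and the pre-operative score has only a descriptive use. The figure of 47% for its SD assumes normality and that recruits are the lowest 20%.

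The size of the benefit is an assumption throughout. It is 0 to about 5% off the standard error, and power of about 90% rising to at most about 93% at 198 per arm if 9.2 is taken as the residual SD. A reader should not infer that the primary analysis is biased, that the trial is underpowered or that the sample size is wrong.

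**What to change.** Before any comparison by arm is seen, pre-specify the primary ANCOVA of one-year OKS with arm, six-week OKS and pre-operative OKS (both continuous), and centre. Centre belongs in the model because randomisation is stratified by it; the article does not say whether it will be included. Keep the change-score summaries as descriptive.

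State a rule for missing pre-operative scores: mean imputation that ignores arm, or a missing indicator, so that no randomised patient is dropped. As the scores are retrieved after the event, retrieve them in the same way for both arms.

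The cost is one extra continuous covariate, the centre terms and the missing-value rule. No new data collection is needed, and recruitment was still open when the article was submitted. If pre-operative OKS proves uninformative, about one degree of freedom is lost.

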### Ethics

TRIO has received ethical approval from the National Research Ethics Service, South East Scotland Research Ethics Committee 01 in April 2013 (REC reference: 13/SS/0051).

## Trial status

Recruitment to TRIO commenced in September 2013 and is on-going at the time of manuscript submission. The expected time of recruitment completion is March 2015.

## Abbreviations

ANCOVA: analysis of covariance; CTIMP: Clinical Trial of an Investigational Medicinal Product; EQ-5D: EuroQol 5 Dimension score; NICE: National Institute for health and Care Excellence; OA: osteoarthritis; OKS: Oxford Knee Score; PROMS: Patient Reported Outcome Measures; QALYs: Quality Adjusted Life Years; RCT: randomised controlled trial; TKA: total knee arthroplasty; TKR: knee replacement; TUG: Timed-get-up-and-go test; VAS: Visual Analogue Scale.
